#### Statistical Analysis

Patient medication changes and clinical events will be compared to 100 matched historical controls. Controls will be patients with HFrEF matched on an HF hospitalization in the past year, age within 5 years, sex, race, and comorbidities (coronary artery disease, diabetes mellitus, hypertension, renal disease).

Statistical analysis for clinical end points will be in comparison with matched controls. For survey data, including RPM platform utility and patient symptom assessments, these will be evaluated for change over the trial’s 6-month duration. Continuous variables will be assessed via sample *t* tests, and categorical variables will be assessed via chi-square tests.

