## Introduction

Heart failure (HF) remains a leading driver of morbidity and mortality in the United States, affecting 6.5 million Americans [1]. Despite numerous medical innovations in HF over the past decade, per capita rates of HF hospitalizations have actually increased from 2010 to 2017 [2]. This population is expected to increase by 50% by 2030, placing an increasing burden on the US health care system and highlighting the need for innovations in HF care [3]. HF care also carries significant economic implications, with over US $30 billion spent in direct HF care in 2020, primarily driven by HF hospitalizations, and estimated to double by 2030 [4-6].

Effective HF care requires vigilance for indications of clinical HF decompensation. Failure to detect and manage these indicators can result in unplanned emergency department (ED) visits and hospitalizations. Although patients and care teams attempt to detect signs of impending decompensation with conventional techniques such as daily weight measurements, these approaches have not demonstrated consistent clinical efficacy [7].

Optimal HF care also relies on maximizing guideline-directed medical therapies (GDMTs). Several pharmacotherapies such as renin-angiotensin-aldosterone system inhibitors and beta-blockers have demonstrated mortality benefit in patients with HF with reduced ejection fraction (HFrEF) [8,9]. However, consistent provision of these therapies, at maximally tolerated dosing, does not occur [10]. Logistical challenges of conventional outpatient care contribute to this implementation gap. These include reliance on ambulatory visits for medication titration, which often occur months apart, and insufficient vital sign information to allow for medication up-titration between visits.

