### Study Protocol

Following enrollment, study participants have the Home Hub and sensors shipped to their homes. Once the kit is delivered, the technical support team will reach out to assist with home monitoring and sensor setup.

As part of the study, patients will take measurements daily from all study sensors. The first 7 days for each patient will be a run-in period where patient data is collected. If sufficient data is collected and transmitted, study participants will transition to the active management phase. Sufficient data is defined as transmission from both BP cuff/weight scale and ballistocardiograph sensors in at least 4 of the 7 days. If minimum requirements are not met, patients are continued in the run-in period for an additional week (up to 3 weeks maximum). Technical support will contact patients to determine if lack of transmission represents a technical issue versus nonadherence. If patients were unable to meet minimum data requirements after 3 weeks, then they were disenrolled from the study.

Following run-in period completion, study participants will enter the 6-month active management phase of the study. A designated research nurse is responsible for daily monitoring of the RPM clinical interface. This includes monitoring the RPM clinical interface daily for clinical alerts, contacting patients to assess clinical status in response to alerts, and escalating to the patient’s HF cardiologist if clinical status warrants management changes. This research nurse will also be responsible for contacting study participants for issues with data transmission or poor adherence to patient data collection.

On a monthly basis, enrolled patients will have their clinical data reviewed by a multidisciplinary team including a triaging nurse and an HF cardiologist. The purpose of these reviews is to assess participant’s clinical status and adherence to data transmissions, and to identify opportunities for optimized medical management, including maximizing GDMT. RPM platform monitoring is outlined in Figure 2.

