#### Power Calculation

##### Medication Changes

This trial is powered at 99% to assess for 50% more medication changes in the study arm compared to historical controls. We will use a type I error of 0.05, assuming Poisson distribution [17]. This medication change rate was selected based on prior work in the CHAMPION trial, in which monitored patients had over double the number of medication changes (n=2468 for 270 patients vs n=1061 for 280 patients; *P*<.001) [18].

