## Results

This prospective trial began enrollment in March 2020 and anticipates enrollment completion by June 2022, with trial completion by December 2022.

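### The matching rule for the historical controls fixes neither time since the HF event nor calendar period, so both are confounded with the RPM effect, in a direction the document does not settle

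*Protocol article*

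**What the plan says.** All references are to the protocol article.

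- **Comparison (Statistical Analysis).** "Patient medication changes and clinical events will be compared to 100 matched historical controls". The rule is: "Controls will be patients with HFrEF matched on an HF hospitalization in the past year, age within 5 years, sex, race, and comorbidities", the comorbidities being coronary disease, diabetes, hypertension and renal disease. The Medication Changes outcome sends the reader to the statistics section for the matching method, so this is where the article sets it.
- **Participants' entry (Textbox 1).** They qualify by a hospital admission or an emergency department attendance for HF at any point in the preceding 12 months.
- **Participants' clock (Study Protocol).** Equipment is shipped and set up, and a run-in of 1 to 3 weeks follows. On failing it: "If patients were unable to meet minimum data requirements after 3 weeks, then they were disenrolled from the study". Only then does follow-up start: "Following run-in period completion, study participants will enter the 6-month active management phase of the study".
- **Calendar time.** For participants (Results): "This prospective trial began enrollment in March 2020 and anticipates enrollment completion by June 2022, with trial completion by December 2022". No period is given for the controls. The only background trend stated is in the Introduction: "per capita rates of HF hospitalizations have actually increased from 2010 to 2017".
- **What depends on the controls.** GDMT dose category from month 0 to month 6, number of medication changes, and clinical events. Medication changes is the controlled comparison the trial is powered for: "This trial is powered at 99% to assess for 50% more medication changes in the study arm compared to historical controls".

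**The concern.** A comparison with historical controls is interpretable only if both groups start the clock at a comparable point. Here one participant may start a few weeks after an HF event and another a year later. A control satisfies the rule with a hospitalization anywhere in the past year. If event risk or prescribing activity varies with time since the event (an assumption; the article gives no figures), the rate in each group depends on where its clock starts, and matching on age, sex, race and comorbidity does not correct that.

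Three further asymmetries follow from the text. Controls are historical with no stated period, so any change in practice or admission rates falls entirely between the groups. Participants can enter through an emergency visit alone, while the matching rule names only hospitalization. Participants must show that they can transmit data, and controls face no equivalent filter.

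At stake are the one powered controlled comparison and the HF-hospitalization result, which the article plans to read as a possible trend.

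**Working it through.** **1. The plan's own power figure.** Inputs from Power Calculation, Medication Changes: 99% power, rate ratio 1.5, "We will use a type I error of 0.05, assuming Poisson distribution". The control rate is not stated. I take the reference trial's control arm as an assumption: 1061/280 = 3.79 changes per patient. For n = 100 per group,

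z = ln(RR) / √[1/(nλ) + 1/(nλ·RR)], power = Φ(z − 1.96).

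With λ = 3.79 and RR = 1.5, z = 0.4055/0.0663 = 6.11 and power exceeds 0.9999. Power of exactly 99% two-sided needs λ ≈ 1.86 (z = 0.4055/0.0946 = 4.29). The stated 99% is therefore attainable, and I carry both rates forward.

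**2. What that power detects when RPM does nothing.** The same formula applies to a difference between groups of any origin. For a background ratio of 1.2:

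- λ = 3.79: z = 0.1823/0.0696 = 2.62, Φ(0.66) = 75%.
- λ = 1.86: z = 0.1823/0.0993 = 1.84, Φ(−0.12) = 45%.

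Ratios of 1.1 and 1.3 give 27% and 97% at 3.79, and 15% and 77% at 1.86. A ratio of 0.8 gives a significant decrease with probability 0.825 at 3.79. These figures assume Poisson variance. If the variance were twice the mean, z at 3.79 and ratio 1.2 would fall to 2.62/√2 = 1.85, and the probability to about 46%.

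**3. Clock misalignment and HF hospitalization.** Assume the hazard is M times its later level for the first 3 months after the event, follow-up lasts 6 months, and RPM has no effect. Expected events, in units of the later monthly hazard, are 6 + (M − 1) × (mean months of follow-up that fall in the early period).

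- Follow-up from the event: 3 early months.
- Start uniform over 0 to 12 months: 3²/24 = 0.375.
- The same plus a run-in of L months: (3 − L)²/24, which is 0.320 for 1 week (L = 0.23) and 0.222 for 3 weeks (L = 0.69).
- Start uniform over 0 to 1 month, run-in ignored: 2.5.

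Rate ratio, participants over controls:

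| Scenario | M = 1.5 | M = 2 | M = 3 |
|---|---|---|---|
| A. Controls from the event; participants 0–12 months plus run-in | 0.815–0.821 | 0.691–0.702 | 0.537–0.553 |
| B. Controls 0–12 months; participants 0–12 months plus run-in | 0.988–0.996 | 0.976–0.991 | 0.955–0.984 |
| C. Controls 0–12 months; participants 0–1 month | 1.17 | 1.33 | 1.63 |

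Examples: A with M = 2 and a 1-week run-in is 6.320/9 = 0.702; without a run-in it is 6.375/9 = 0.708. C with M = 2 is 8.5/6.375 = 1.33. Adding the run-in to C lowers the early months to between 2.27 and 1.81, and the range becomes 6.905/6.1875 = 1.12 to 10.54/6.75 = 1.56. With a 1-month early period, A weakens to about 0.92, 0.86 and 0.75.

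**4. Size against the effect sought.** The HF Hospitalizations power section needs 1054 per group for 80% power. At 100 per group, z = (1.960 + 0.842) × √(100/1054) = 0.863 and power = Φ(0.863 − 1.960) ≈ 14%. A misalignment bias as large as in A or C could exceed the effect being looked for.

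**The case against.** **The bias need not favour RPM.** A reader might infer that the early high-risk period and background trends will be counted as RPM benefit. The document does not support that. It requires controls to be followed from their hospitalization, which is stated nowhere. A past-year criterion reads at least as naturally as a look-back from an index date, parallel to the participants' own 12-month criterion, and scenario B then leaves almost no bias. Scenario C reverses it. For medication changes, if titration is heavier soon after an event, controls followed from the event would show more changes, which works against RPM. The one stated trend, rising admissions, would if it continued give older controls lower rates, again against RPM. This objection stands, and it removes any claim about direction.

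**Some alignment exists.** The shared past-year window is a coarse alignment on time since event, so it is wrong to say there is none. It still lets one group start near the event and the other up to a year later.

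**The run-in is not lost follow-up.** It precedes the 6 months, so expressing 1 to 3 weeks as a share of 26 weeks says nothing about bias. Its delay alone is scenario B. Its selection of transmitters is a separate matter that the document does not let one quantify.

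**This may be detail left to a fuller document.** Partly fair: an index-date rule could sit elsewhere. But the article states a specific matching list, points to that section for the method, and compares dose category from month 0 to month 6 with controls, for whom no month 0 is defined. The rule as stated, if followed, permits all three scenarios.

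**Hospitalization is admittedly underpowered.** True, and the article says so. That limits the consequence for this endpoint, but a trend read without power is easily produced by bias. Medication changes has no such protection.

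**Conclusion.** The concern holds in a limited form. The stated matching rule leaves time since event (beyond a 12-month window), calendar period, type of qualifying event and run-in selection uncontrolled, so all of these are confounded with RPM. The sign of the resulting bias cannot be determined from the document.

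Under assumed early hazards of 1.5 to 3 times for 3 months, the HF-hospitalization rate ratio under no effect runs from about 0.54 to 1.63, depending mainly on how controls are indexed, and lies near 1 if both groups are indexed over the same 12 months. For medication changes, a 20% background difference would be declared significant 45% to 75% of the time, given Poisson variance and 1.86 to 3.79 changes per control. The hazard multiples, entry patterns and control rates are assumptions. A reader might also infer from the March 2020 start that care use was atypical, but the document gives no figure or direction for this, so it adds nothing beyond the unstated calendar gap.

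**What to change.** Define a control index date: the same number of days after the control's qualifying event as the matched participant's start of the active phase is after theirs. Require the control to be alive, out of hospital and eligible on that date. Use the same type of qualifying event in both groups, and follow both for 6 months from the aligned date, which also supplies the missing month 0 for dose category. Before any control data are extracted, fix the controls' calendar window as close to the trial period as possible, and report the remaining gap with the results.

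The cost is a more complex record query and a somewhat smaller control pool. Concurrent controls from the same clinic would reduce the calendar problem, but the same clinicians would treat both groups and non-enrolled patients may differ from enrolled ones. They are an option to weigh, not a requirement. Indexing does not reproduce the selection of patients who can transmit data, so that should be stated as a remaining limitation.

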**Methods:**

Nov-RPM-HF is a 100-patient single-center prospective trial, evaluating patients over 6 months. The outcomes will include patient adherence to data collection, patient/clinician-perceived utility of the RPM platform, medication changes including the titration of guideline-directed medical therapy to target doses, heart failure symptoms/performance status, and unplanned heart failure hospitalizations or emergency department visits.

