## Methods

### Overview

The Nov-RPM-HF trial is a single-center prospective study of an RPM platform and its adoption, clinical utility, and ability to optimize GDMTs and reduce unplanned acute care events among patients with HFrEF. Specifically, the trial will evaluate patient adherence with passive and active data collection, patient-perceived usability and utility of the RPM platform to monitor their health status, clinician-perceived usability and utility of the RPM platform for HF management, clinical utility of the RPM clinical alerts, impact of RPM on medication changes and titration of HF GDMT, and impact of HF RPM on clinical outcomes (ED visits, hospitalizations).

Full inclusion and exclusion criteria are summarized in Textbox 1. Inclusion criteria include history of HFrEF with a HF hospitalization or ED visit in the last 12 months. This criteria selects for a HFrEF population with a baseline event rate that mirrors the trial population in the CHAMPION (CardioMEMS Heart Sensor Allows Monitoring of Pressure to Improve Outcomes in NYHA Class III Heart Failure Patients) trial. Such an event rate should allow for increased power to detect clinical outcomes among our study population. Prior noninvasive RPM trials have included a relatively stable population of patients with HF with low clinical event, and this was thought to have contributed to the inability to demonstrate clinical efficacy [13]. End-stage HF with a life expectancy <1 year or requiring advanced therapies including left ventricular assist devices or cardiac transplantation were excluded. Patients with barriers precluding them from obtaining monitored data (eg, wearable defibrillator use preventing ballistocardiograph sensing) were also excluded.

Inclusion and exclusion criteria.

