##### HF Clinical Events

The study’s primary clinical end point is HF hospitalizations. Secondary clinical events include other unplanned hospitalizations and ED visits. Clinical events will be obtained through monthly electronic health record review by the research team and with monthly patient surveys. All hospitalizations will be adjudicated by the clinical team as either HF or other unplanned hospitalizations. Clinical end points will be compared to those of matched controls.

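### Participants may enter on an ED visit, but the control rule names only an HF hospitalization, so ED-only entrants have no like-for-like control and baseline risk can differ between the groups

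*Protocol article*

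**What the plan says.** **Entry of participants.** The Overview in Methods states: "Inclusion criteria include history of HFrEF with a HF hospitalization or ED visit in the last 12 months". Textbox 1 repeats the two routes, requires NYHA class II-IV, and excludes among others patients on advanced HF therapies, on chronic dialysis, or in hospice or with a life expectancy under one year.

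**Run-in.** The Study Protocol section adds a selection step after enrollment: "If patients were unable to meet minimum data requirements after 3 weeks, then they were disenrolled from the study".

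**Controls.** The Statistical Analysis section says: "Patient medication changes and clinical events will be compared to 100 matched historical controls". It then gives the rule: "Controls will be patients with HFrEF matched on an HF hospitalization in the past year, age within 5 years, sex, race, and comorbidities". Four comorbidities are listed: coronary disease, diabetes, hypertension and renal disease. The rule names no ED-visit route, LVEF value, NYHA class or baseline GDMT dose, and does not mention the exclusions of Textbox 1.

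**Use of the controls.** The HF Clinical Events section says: "Clinical end points will be compared to those of matched controls". The Medication Changes section compares the number of changes and the change in proximity to target dose with the same controls, and refers the reader to the statistical section for the matching method.

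**The concern.** The trial has no randomized comparator, so its comparative results depend on how alike these 100 controls are to the participants. The Overview itself treats the qualifying event as prognostic: it was chosen to obtain a particular baseline event rate. A different qualifying event for controls therefore alters the rate being compared.

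The Power Calculation section concedes that HF hospitalizations are underpowered and says they will be collected to look for a positive trend. A modest difference in baseline risk could produce, or hide, such a trend. The number of medication changes, the comparison with controls for which power is claimed, uses the same controls.

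**Working it through.** **1. The two readings of *matched on*.**

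- Reading A: every control had an HF hospitalization. An ED-only participant is compared with a patient who had been admitted.
- Reading B: the control shares the participant's hospitalization status, as with sex or race. An ED-only participant gets a control without an HF hospitalization. Because ED visits are not a matching factor, that control may have had no acute HF event.

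Neither reading secures a control whose qualifying event was an ED visit.

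**2. Stated power for medication changes.** Inputs: 100 per group, ratio 1.5, type I error 0.05 (two-sided assumed), Poisson counts, and the cited control rate 1061/280 = 3.79 per patient.

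Power = Φ( ln RR / √(1/(nλ₀) + 1/(nλ₁)) − 1.96 )

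- λ₀ = 3.79, λ₁ = 5.68: standard error 0.0663; 0.4055/0.0663 − 1.96 = 4.15; power above 99.9%.
- λ₀ = 1.89 (half that rate, an assumption about length of follow-up): standard error 0.0938; 4.32 − 1.96 = 2.36; power 99.1%.

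The stated 99% is reproduced. It presumes comparable groups.

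**3. HF hospitalizations under Reading A, with no RPM effect.** Let f be the share of participants who entered on an ED visit alone, and r their HF hospitalization rate relative to patients with a prior HF hospitalization. Both are assumptions.

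Null rate ratio = 1 − f(1 − r)

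| f | r = 0.5 | r = 0.7 | r = 0.8 | r = 1.0 |
|---|---|---|---|---|
| 10% | 0.95 | 0.97 | 0.98 | 1.00 |
| 20% | 0.90 | 0.94 | 0.96 | 1.00 |
| 30% | 0.85 | 0.91 | 0.94 | 1.00 |
| 40% | 0.80 | 0.88 | 0.92 | 1.00 |

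If r exceeds 1 the bias reverses: f = 20% and r = 1.2 give 1.04.

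**4. Scale.** The article gives 1054 per group for 80% power but neither the event rate nor the ratio behind it, so that figure cannot be reproduced. Solving the formula in step 2 for the ratio, with assumed control rates of 0.2-0.6 events per patient, gives about 0.74-0.85. Only the upper end of the assumed biases (ratios of 0.80-0.85) reaches that range.

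With 100 per group and no RPM effect, the chance of a significant result favouring RPM is nominally 2.5%. At a null ratio of 0.80 it is 12.6% (control rate 0.3) to 18.2% (control rate 0.5). At 0.94 it is 4.2% to 4.9%.

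**5. Medication changes under Reading A.** If ED-only entrants also need fewer changes, by the same factor r, a true ratio of 1.5 appears as 1.5 × [1 − f(1 − r)]: from 1.5 × 0.98 = 1.47 down to 1.5 × 0.80 = 1.20. At 3.79 changes per control, power is about 75% at 1.20 and above 99.9% at 1.47. This works against RPM.

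**6. HF hospitalizations under Reading B.** Let u be the relative rate in the non-hospitalized controls. The null ratio is [(1 − f) + f·r] / [(1 − f) + f·u]. It is 1.00 if u = r. For illustration, r = 0.7 and u = 0.5 give 0.97/0.95 = 1.02 at f = 10% and 0.88/0.80 = 1.10 at f = 40%, against RPM.

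**The case against.** A reader might infer that controls are sicker by construction and that every comparison therefore favours RPM. The documents do not support that, for four reasons.

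- Reading A is plausible but not certain. The phrase stands in a list with sex and race, where matching means sharing the participant's status. This stands, but Reading B still gives ED-only entrants no equivalent control.
- Participants must be NYHA II-IV and come from an advanced HF clinic. Neither is a stated requirement for controls, and both would make participants the sicker group. This stands.
- Sicker, recently admitted controls may have more medication changes, which would count against RPM. This stands.
- That dialysis, advanced-therapy or hospice patients may serve as controls is inferred from silence in a condensed article. The full protocol may apply the exclusions. Controls must also have HFrEF, which Textbox 1 defines by LVEF, so that criterion arguably carries over. This stands, and the point does not depend on the exclusions.

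A further tempting reading is that the mismatch accounts for most of the planned effect on hospitalizations. That holds only at the upper end of assumed ranges, and no adequately powered hospitalization claim is planned. Comparing change in dose category, not final dose, also partly offsets the lack of matching on baseline dose.

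The difference between the two stated entry events remains. It is in the text, in the section to which the article refers for the matching method.

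**Conclusion.** The control rule does not mirror the entry rule. ED-only entrants have no like-for-like control under either reading, and LVEF, NYHA class and baseline GDMT dose are not matched, so baseline risk can differ in every comparison with controls.

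If all controls were hospitalized, HF hospitalizations would probably be biased toward RPM. The null ratio is about 0.80-0.98 for f of 10-40% and r of 0.5-0.8, and 1.00 if the rates are equal. Medication changes could be biased against RPM. These sizes rest wholly on assumed values of f and r, and the document does not settle the net direction.

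Two further asymmetries belong here. The article does not state that the prognostic exclusions apply to controls. The run-in disenrollment selects participants only; this one is explicit, and for clinical events it would plausibly favour RPM.

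**What to change.** Revise the control rule in the Statistical Analysis section:

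1. Match on type of qualifying event in the prior 12 months: HF hospitalization, or ED visit only.
2. Give each control an index date, and require at that date every Textbox 1 criterion that the record can show, including the prognostic exclusions.
3. Adjust the comparisons for LVEF and baseline GDMT dose. The trial needs LVEF for eligibility and baseline dose for its own outcome; both should be readable from the record for controls.
4. Report the run-in selection as a remaining limitation, and include the clinical events of disenrolled patients in a sensitivity analysis where the record allows.

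Reporting the ED-only share would show how much the first item matters.

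Cost: a revised selection query, some extra chart screening and a somewhat smaller pool of controls. No additional participants are needed.

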Remote patient monitoring (RPM) aims to address these gaps in current HF care. RPM is a strategy that allows care teams to monitor and manage patients outside of traditional in-person health care encounters. The strategy could enhance current efforts for more rapid medication titration and avoidance of clinical decompensation and unplanned acute care visits. RPM has demonstrated a reduction in HF hospitalizations, but only by using an invasive hemodynamic patient sensor (CardioMEMS) [11]. RPM strategies using noninvasive patient sensors such as blood pressure (BP) cuffs, scales, and wearable biosensors have reduced cost, lower risk, and greater applicability to the HF population. However, the clinical evidence supporting noninvasive RPM is mixed, with the majority of clinical trials failing to demonstrate a similar clinical benefit [12]. This lack of clinical efficacy in trials is likely attributable to multiple factors, including poor patient adherence [13], lack of clinically actionable patient data and alerts [14], and lack of clinician engagement [15].

The field of noninvasive RPM continues to evolve, with recent advances in data collection and monitoring now demonstrating improved predictive power for clinical decompensation [16]. However, there is a paucity of studies evaluating these emerging tools as part of RPM interventions.

The Novel Diagnostic Tools for Remote Patient Monitoring in Heart Failure (Nov-RPM-HF) Trial aims to address these limitations through the design and evaluation of a novel RPM platform for HF management that incorporates these emerging data collection tools. The trial will evaluate the perceived utility of the RPM platform, its impact on timely GDMT optimization and medication changes, and its impact on unplanned ED visits and hospitalizations.

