#### Outcomes

Trial outcomes were designed to both directly evaluate the perceived utility of the RPM platform and to assess its impact on clinical outcomes.

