##### Patient-Perceived Usability and Utility of RPM Platform

Patients’ assessment of the RPM platform utility and usability will be assessed through a series of surveys (survey timeline in Multimedia Appendix 1). Surveys will be conducted at 2, 4, and 6 months. Surveys will have scaled numerical responses 1 to 7, with 17 total questions. Questions will assess RPM platform components (scale, BP cuff, ballistocardiograph) usability, platform setup, and the platform’s perceived utility in augmenting clinical care. The sum of the numeric responses for each question will combine into an “overall utility score.” This score will be assessed for change throughout the study duration for each participant. Surveys will be reviewed at the time of submission by the research nursing group. Patients will be contacted regarding any significant RPM platform concerns. Scores will also be analyzed to assess for RPM platform strengths/weaknesses and to evaluate for change in perceived utility over the trial duration.

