##### Clinician-Perceived Usability and Utility of RPM Platform

Along with patients, clinicians will also be assessing the RPM platform’s utility and usability through a series of surveys (survey timeline in Multimedia Appendix 1). Surveys will be conducted at 3 and 6 months, with scaled numerical 1 to 7 ratings of 14 components of the RPM platform, with a focus on the clinical interface.

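### Perceived utility of the platform is a named aim, but the only inference stated for the platform ratings is change between post-start surveys; the level of the ratings should be the main estimate

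*Protocol article*

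**What the plan says.** The Introduction states the aim: "The trial will evaluate the perceived utility of the RPM platform". The Overview of the Methods lists usability and utility as perceived by patients and by clinicians among the things to be evaluated. The Outcomes section adds: "Trial outcomes were designed to both directly evaluate the perceived utility of the RPM platform and to assess its impact on clinical outcomes".

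The Statistical Analysis section gives one rule for all survey data: "For survey data, including RPM platform utility and patient symptom assessments, these will be evaluated for change over the trial’s 6-month duration". The tests follow: "Continuous variables will be assessed via sample *t* tests, and categorical variables will be assessed via chi-square tests". The section on patient-perceived utility sums 17 items, each scored 1 to 7, into an overall utility score and says of it: "This score will be assessed for change throughout the study duration for each participant".

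On timing, the patient section says "Surveys will be conducted at 2, 4, and 6 months" and the clinician section says "Surveys will be conducted at 3 and 6 months, with scaled numerical 1 to 7 ratings of 14 components of the RPM platform".

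Three other places bear on the level of the ratings or on utility. The patient section also has scores examined for the platform's strong and weak points. The Discussion says clinician survey results will be broken down by platform component and set beside the actions that alerts led to. The section on alert utility reports the share of alerts that prompted action.

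For KCCQ-12, the section on HF symptoms and performance status gives a month-0 assessment and promises absolute results as well as change.

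**The concern.** Whether users find the platform useful is a question about the level of their ratings. The stated inference is about movement in those ratings after use has begun. The two can disagree in both directions. Steady, favourable ratings give a non-significant result. Poor ratings that drift up give a significant improvement, and good ratings that slip slightly give a significant decline.

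The single rule for survey data suits KCCQ-12, where a month-0 score exists and improvement in health status is the question. It does not suit opinions of a product that the respondent had not used before the trial. At stake is whether the headline inference for a named aim answers that aim.

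**Working it through.** **Is there a planned figure to reproduce?** The article gives no power, effect size or threshold for perceived utility. The nearest survey figure is the KCCQ power: n = 100, change 6, SD 20, type I error 0.05, stated power 84%.

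- One-sample (paired) t test on change: noncentrality = 6 / (20/√100) = 3.0; critical t on 99 df = 1.984; two-sided power = 84.4%. This reproduces the stated 84%.
- Two-sample t test, 100 per group: 56.4%. This does not.

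So within-patient change is the form of survey test that fits the article's own arithmetic. The article names only t tests and does not state the paired form.

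**Scale.** From the patient section: 17 items scored 1 to 7. The sum runs from 17 × 1 = 17 to 17 × 7 = 119, with midpoint 17 × 4 = 68.

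**What the change test responds to.** With D = later score − first score, t = mean(D) / (SD(D)/√n). If ratings are constant at any level, the expected D is 0 and the test rejects at its type I error rate. The level cancels.

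**Simulation of constant ratings.** Assumptions not in the article: between-patient SD 10, within-wave SD 8, n = 100, no missing surveys, 4,000 runs.

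| Constant rating | Sum score | Change test rejects | Mean at month 6 | Month-6 mean vs 68 rejects |
|---|---|---|---|---|
| 6 of 7 | 102 | 5.1% | 102 | 100% (above) |
| 2 of 7 | 34 | 5.1% | 34 | 100% (below) |

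The 5% in both rows does not depend on the assumed SDs. The comparison with 68 is only an illustration, because the article sets no such benchmark.

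**Small drifts.** Take a shift of 0.4 per item, 17 × 0.4 = 6.8 points: for example 2.4 to 2.8 (still poor) or 5.9 to 5.5 (still good). Assume SD 20 for the sum and correlation 0.6 between waves.

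- SD(D) = 20 × √(2 × 0.4) = 17.9
- SE = 17.9/10 = 1.79
- noncentrality = 6.8/1.79 = 3.80
- power about 96%

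Simulation on the bounded 17–119 scale gave 97% for the rise and 96% for the fall. Over SD 15–25 and correlation 0.3–0.8 the range was 61–100%. These figures rest wholly on the assumed SD, correlation and drift.

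**What a level estimate would deliver.** 95% CI half-width for the month-6 patient mean = 1.984 × SD/√100.

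| Assumed SD of sum | Half-width (sum) | Per item (÷ 17) |
|---|---|---|
| 15 | 3.0 | 0.18 |
| 20 | 4.0 | 0.23 |
| 25 | 5.0 | 0.29 |

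This assumes that all 100 patients respond. The number of responding clinicians is not given, so no half-width is worked out for them.

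**Time span.** Patients: first survey month 2, last month 6, so the longest change is 6 − 2 = 4 months. Clinicians: 6 − 3 = 3 months. Neither covers the 6 months named in the Statistical Analysis section.

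**The case against.** The best case for the plan has five parts.

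1. *Levels are used elsewhere.* Strengths and weaknesses can only be read from levels, and so can clinician ratings by component. The share of alerts acted on is a further measure of utility that does not depend on change. This stands. A reader might infer that a well-liked and a disliked platform would be indistinguishable in the trial's results, or that change is the only analysis of the clinician survey. The article supports neither inference. The indistinguishability is confined to the planned test.

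2. *Change is a question the article itself asks.* This also stands. Change in perceived utility is a legitimate secondary question, and nowhere does the article say that no change means no utility.

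3. *There is no baseline because nobody can rate a platform before using it.* Correct. A reader might take the missing month-0 survey for a design fault, and it is not one. The lack of a baseline is a reason for not making change the main quantity.

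4. *The size is partly circular.* A test of change rejects at 5% under no change by construction. Setting its rejection rate against that of a test versus the midpoint and calling the gap lost power would compare two different hypotheses, one of which uses a benchmark the article never states. No loss of power is claimed here.

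5. *Means and intervals are details a condensed article leaves to the full documents.* This holds for the technical detail. It does not cover the choice of quantity, which the article does state: change for the overall utility score, but absolute results and change for KCCQ-12.

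**Conclusion.** The point holds as a mismatch between a named aim and the only inference stated for it. The test of change carries no information on level: constant ratings of 6 and of 2 out of 7 both reject at about 5%, whatever the SD. The descriptive breakdowns by item and component soften the consequence but do not give the overall utility score a level estimate as its main result. In addition, the stated 6-month span cannot be observed for platform ratings; at most 4 months can be for patients and 3 for clinicians.

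The conclusion about constant ratings needs no outside figure. The drift percentages and half-widths do rest on assumed SDs, and the drift percentages also on assumed correlations. Perceived utility carries no power claim or decision rule, and the primary clinical end point is unaffected. It is nonetheless a stated aim, and the remedy is nearly free, so the change should be made.

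**What to change.** In the Statistical Analysis section, give platform ratings and KCCQ-12 separate sentences.

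- **KCCQ-12:** leave as it is, with absolute results and change from month 0.
- **Platform ratings, patients and clinicians:** make the mean rating with 95% CI at each wave the main estimate, with month 6 foremost.
- **Change in platform ratings:** keep as secondary, labelled months 2–6 for patients and months 3–6 for clinicians. Amend the sentence on the overall utility score in the patient section to match.
- **Reference value:** optional. If the scale midpoint is used (4 per item, 68 on the patient sum), present it as a convention, since the article does not show the item wording or anchors.

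The surveys, visits and sample stay as they are, and no baseline survey is added. The cost is slightly more reporting. Satisfaction ratings tend to run high, so the level should be read with its interval and not as a pass/fail test.
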